### Allocation Concealment

Participants and the investigators enrolling the participants will not foresee assignment. We will use numbered sealed envelopes in different data collection organizations. Whereas patients and health care staff will be aware of the allocated arm, outcome assessors and data analysts will be kept blinded to the allocation.

### Primary and Secondary End Points

The primary outcomes are service use and healthy days by 12 months based on routine data (admission to psychiatric hospital, time to next hospitalization, time in hospital during this year, and healthy days). The secondary outcomes are service use, coercive incidents, medication, adverse event, satisfaction with care, intervention, and the trial, social functioning, and economic factors. M1 referral is a referral for observation by any physician if he or she considers it likely that criteria for involuntary admission are fulfilled. This sets in motion the process by which the patient is later examined by a second doctor in a psychiatric hospital. This doctor must be a psychiatrist. At this stage, the patient can be admitted voluntarily or involuntarily, or discharged [29]. Data will be collected 12 months after baseline (see Table 2 [30,31]).

**Table 2 table2:** Dummy table for primary and secondary outcomes and end points.

Outcome				Intervention				Control			
				n (%) or mean (SD)		RR^a^ (95% CI^b^)	*P *value	n (%) or mean (SD)		RR (95% CI)	*P *value
**Primary outcome**				DUMMY TABLE - CELLS INTENTIONALLY EMPTY							
	**Service use/healthy days**										
		Admission to psychiatric hospital									
		Time to next hospitalization (days)									
		Time in hospital during this year (days)									
		Healthy time (days)									
**Secondary outcomes**											
	**Service use**										
		Type of admission									
			M1 referral^c^								
			Mental examination								
			Determination of treatment								
			Other								
		Involuntary treatment									
		General hospital treatment									
		Use of private care									
		Length of involuntary psychiatric treatment (days)									
		Length of general hospital stay (days)									
	**Coercion**										
		Coercive incidence									
		Type of coercive incidence									
			Seclusion								
			Physical restraint								
			Intramuscular medication								
			De-escalation								
	**Medication**										
		Type of medication									
			Antipsychotic								
			Antipsychotic + antidepressant								
		Medication									
	**Adverse event**										
		Any (yes)									
		Death (yes)									
	**Satisfaction with care/intervention/trial**										
		Satisfied with care									
		Requested to stop SMS^d^									
		Left the study early									
	**Social functioning**										
		Quality of life									
		Disability support									
	**Economic factors**										
		Direct cost (€)									
		Indirect cost (€)									

^a ^Relative risk.

^b ^Confidence interval.

^c ^Referral for observation.

^d ^Short message service.

The outcomes will be based on register data [30,31] and patients’ subjective evaluations.

### Adverse Event Reporting

Safety assessments will include all adverse or serious adverse events, and subjective symptoms reported by clinical staff or study personnel, participants, or relatives. Adverse event monitoring data will be collected by the following methods: (1) reports from clinical staff or study personnel, and (2) text message, mailing, phone call, or survey after 12 months during the 1-year intervention with the question “Have you experienced any new and serious health problems since you enrolled in the Mobile.Net Study? If yes, please describe them.”

We will provide categories of possible adverse events. Adverse events will be categorized as severe if they are life-threatening or fatal, require or prolong a hospitalization, or result in a major disability. In addition, adverse event may be categorized as unexpected or expected (Table 3).

**Table 3 table3:** Dummy table for number of adverse events.

		Intervention	Control
**Expected severe adverse events**		DUMMY TABLE - CELLS INTENTIONALLY EMPTY	
	Life-threatening or fatal		
	Requiring or prolonging a hospitalization		
	Resulting in a major disability		

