**Expected adverse events**			
	Medical		
	Psychiatric		
	Substance use		

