**Unexpected adverse events**			
	Medical		
	Psychiatric		
	Substance use		

The potential safety concerns about possible psychiatric effects of exposure to a mobile phone have been discussed for more than two decades [32], but published results are still inconsistent and inconclusive [33-35]. As the study intervention is a communication system and provides a method of supporting patients’ adherence in regular mental health services, we do not expect serious adverse events as a result of the intervention. We will analyze treatment-emergent adverse events, defined as all adverse and serious adverse events occurring between randomization and when the patient completes the study.

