### Interim Analysis and Stopping Rules

An independent data safety and monitoring committee will be established. The trial statistician will carry out analyses, blinded to allocation, and report the results to the data safety and monitoring committee. Together with an independent statistician, the data safety and monitoring committee will review efficacy and safety data.

Due to the nature of the data collated on the national register, it is not possible to conduct an interim analysis after the recruitment has started. The information in the register data will be available to the researchers after 1 calendar year (ie, data have a 1-year lag time). However, adverse events, early dropout, nurses’ opinions, and patients’ experiences will be monitored and analyzed throughout the study.

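### The one question quoted for patients about harm is narrower than the adverse events the protocol says participants will report, and its timing is unclear

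*Protocol article*

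**What the plan says.** The section headed Adverse Event Reporting opens with its scope: "Safety assessments will include all adverse or serious adverse events, and subjective symptoms reported by clinical staff or study personnel, participants, or relatives". Two collection methods follow. The first is "reports from clinical staff or study personnel". The second is a direct approach to patients, described as "text message, mailing, phone call, or survey after 12 months during the 1-year intervention with the question" and then the question itself: "Have you experienced any new and serious health problems since you enrolled in the Mobile.Net Study". Patients who say yes are asked to describe the problem.

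The same section defines severe events by threat to life or death, hospitalization, or major disability. Table 3 gives severe events their own rows, and then has separate rows, beginning under "Expected adverse events", for medical, psychiatric and substance-use events that are not severe. The closing paragraph sets the events to be analyzed, "defined as all adverse and serious adverse events occurring between randomization and when the patient completes the study". Under Interim Analysis and Stopping Rules the article adds that "adverse events, early dropout, nurses’ opinions, and patients’ experiences will be monitored and analyzed throughout the study".

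**The concern.** The patient question filters twice, on novelty and on seriousness, before the study team sees anything. All participants leave a psychiatric hospital on antipsychotic medication, so each enters with an existing condition that could worsen. A patient whose long-standing symptoms become more troublesome has nothing new to report. A patient with a mild new symptom has nothing serious to report. Both can truthfully answer no, although the stated scope would include them.

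Having any adverse event is a secondary outcome in Table 2, to be compared between arms. The register data that supply the main outcomes lag by a year, and the article gives this as the reason for having no interim analysis. Adverse event collection is therefore a main source of safety information while the trial runs. If the patient route under-records and the remaining route is open to differences between arms, the comparison of harms is weakened and its direction of error is unknown.

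**Working it through.** No alpha, power, rate or sample size enters this point, so the check is a comparison of what the article promises with what its methods can deliver.

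1. **Scope promised.** Adverse events whether serious or not, and subjective symptoms, from staff, participants or relatives (Adverse Event Reporting, first sentence).
2. **Scope asked of patients.** Problems that are both new and serious (same section, second method). This is a strict subset of item 1.
3. **Scope to be tabulated.** Table 3 has 2 expectedness classes × 3 criteria = 6 severe rows, and 2 expectedness classes × 3 types (medical, psychiatric, "Substance use") = 6 non-severe rows. That is 6 of 12 rows, or half the table, for events below the severe threshold.
4. **What a literal answer can supply.** *Serious* in the question is an undefined lay word, while *severe* is the article's defined grade. A problem that the patient considers serious but that meets no severe criterion would still reach a non-severe row. The patient route therefore supplies some non-severe events. It omits those the patient thinks minor and those that are a worsening of something already present.
5. **Who supplies the rest.** The first method, staff and study-personnel reports, has no stated limit on seriousness, novelty or timing. Relatives are named as a source, but neither method says how they are asked.
6. **Is that route even between arms?** Staff and participants are not masked (Randomization and Masking). Ethics Issues itself warns that nurses may favor one group. Intervention patients are encouraged to contact researchers or staff about adjusting messages (Intervention Group), and Control Group describes no matching prompt. Ascertainment could differ by arm, in a direction that cannot be fixed in advance.
7. **Timing.** The phrase places the contact both after 12 months and within the 1-year intervention. There are at least two readings:
   - *(a) All modes used only after 12 months.* Messages run for up to 12 months, so no patient is asked until that patient's own exposure is over. The question then adds nothing to monitoring during that exposure.
   - *(b) Text messages, mailings or calls during the year, and a survey at 12 months.* This agrees with the monitoring promised under Interim Analysis and Stopping Rules, but the contact times are not stated.
8. **Trial-level consequence of reading (a).** Recruitment runs from November 2011 to December 2012. The first 12-month answers fall due in November 2011 + 12 months = November 2012. The last messages could go out until December 2012 + 12 months = December 2013. Some patient answers would therefore arrive while later participants are still receiving messages.

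**The case against.** The strongest reply is that the patient question is only one of two routes. Staff reports are unrestricted and can supply both non-severe events and monitoring during the year. This stands: a reader might infer that the promised events and monitoring cannot be obtained at all, and the article does not support that. The gap is in what patients themselves report.

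Other stronger inferences also fail:

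- **That the plan undertakes to record worsening.** It never uses the word. Worsening is covered only by inference from the all-events scope.
- **That the question captures no non-severe events.** Step 4 shows that it can capture some. The article also says it will provide categories of possible adverse events, and how these are presented may be left to the full protocol.
- **That patients are asked just once, late.** The phrase is ambiguous, and reading (b) is a natural one.
- **That the messages are unsolicited, so worsening is the likeliest harm.** Patients choose content, timing and frequency, and can stop. The article gives no ranking of likely harms.
- **That harm would go unseen.** Readmission, involuntary treatment, coercion, death, requests to stop messages and early leaving are all recorded.

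It can also be objected that repeated scheduled texts to controls would use the intervention's own medium in an arm meant to receive standard care. That is a fair cost, and the point does not depend on such contacts.

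What survives is the mismatch inside one section between the scope promised from participants and the question put to them, and a timing phrase that cannot be followed as written. Unrestricted staff reporting does not repair the first, because it is unmasked and depends on contact with services.

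**Conclusion.** The point holds in this limited form. The quoted patient question is narrower than the scope stated for participants and narrower than half of Table 3. Followed as written, it would under-record events patients regard as minor and worsening of existing illness, and leave these mainly to unmasked staff reports. The timing phrase needs to be reconciled with the promise of monitoring throughout. Only under reading (a) does the patient route contribute nothing during a patient's own exposure.

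The size of the under-recording cannot be computed, because the article gives no event rates. The conclusion assumes that patients answer the question literally and that no broader question to patients exists in a full protocol not shown. The admission outcome is unaffected. What is at stake is a secondary outcome and the reliability of the harms comparison, so a change is worth making but is not critical.

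**What to change.** - Reword the question for both arms along these lines: *Since enrolling, have you had any new health problem, or has any existing physical, mental health or substance-use problem become worse?* Keep the free-text description.
- Let the study team, not the patient, grade severity with the criteria already given under Adverse Event Reporting.
- Replace the timing phrase with a clear statement of when and by which mode patients are asked, consistent with Interim Analysis and Stopping Rules and the same in both arms.
- State how relatives' reports are collected, or remove relatives as a named source.

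The cost is one reworded question and more non-serious reports to classify. Extra scheduled contacts during the year are optional: they would strengthen patient-reported monitoring, but they add contact to the control arm, and the sponsor should weigh that against the pragmatic design.

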**Unexpected severe adverse events**			
	Life-threatening or fatal		
	Requiring or prolonging a hospitalization		
	Resulting in a major disability		
**Expected adverse events**			
	Medical		
	Psychiatric		
	Substance use		
**Unexpected adverse events**			
	Medical		
	Psychiatric		
	Substance use		

The potential safety concerns about possible psychiatric effects of exposure to a mobile phone have been discussed for more than two decades [32], but published results are still inconsistent and inconclusive [33-35]. As the study intervention is a communication system and provides a method of supporting patients’ adherence in regular mental health services, we do not expect serious adverse events as a result of the intervention. We will analyze treatment-emergent adverse events, defined as all adverse and serious adverse events occurring between randomization and when the patient completes the study.

### Statistical Analysis Plans

#### Sample Size and Power Calculations

The study has been powered for the primary outcome measure. We have systematically searched for but not found any directly relevant published work. In London, for example, 65% of potentially eligible people had been admitted to the hospital in the past 12 months [36]. Our aim in Finland will be to reduce use of acute care by at least five percentage points (a relative risk of 0.92). To do this with 80% power at a 5% 2-sided significance level, we would require 1511 participants in each of the two arms (Stata v10; StataCorp LP, College Station, TX, USA).

#### Statistical Tests

The primary outcome will be relative risk of admission to psychiatric inpatient services (Table 2). Secondary outcomes will involve calculation of relative risk or mean differences and their corresponding 95% confidence intervals. To evaluate the clinical outcomes of the study, we will use both descriptive and inferential statistics. Descriptive statistics will be used to evaluate outcomes at the end point and differences between individuals and groups by exploratory analyses (chi-square tests, *t *test or Mann-Whitney *U *test, and nonparametric bootstrap methods for skewed cost data). The principal analysis will compare the primary and secondary outcome measures at 12 months comparing for baseline (preintervention) measures using analysis of covariance.

### Subgroup Analysis Planned

We will analyze subgroups for the primary outcome of people with schizophrenia-like illness compared with others who need antipsychotics. The direct and indirect costs of implementing this service will be examined through the prospective collection of staff time and resource requirements. Total costs of implementing the service will be estimated through local salary and overhead costs and by reference to nationally agreed-upon and unit costs. The cost effectiveness of the approach will be calculated through incremental cost-effectiveness ratios of costs per nonattendance avoided.

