### Interventions

#### Intervention Group

The intervention group will receive semiautomatic SMS messages after their discharge from psychiatric inpatient care. The intervention is patient led rather than researcher led to increase acceptability of the prompt. Therefore, during the discharge process from psychiatric hospital care, patients will choose text message content areas related to their medication and follow-up appointments. Additionally, they will be able to choose messages related to other daily issues (eg, hygiene, physical exercise, nutrition, daily routines, clothing, safety, communication, taking care of pets, following rules, hobbies, work or other activities, household tasks, symptom management, or other supporting messages). Timing, frequency, and conditions under which interventions will be withheld will be decided by the patient. The content of these messages had been designed by patients in a consumer association, and by health care professionals in hospital wards and outpatient clinics. The SMS messages will continue for the duration of the study period (12 months) or until participants no longer want to receive the messages. We do not envisaged that the intervention will interfere in any way with routine outpatient care. Patients will be encouraged to contact the researchers or health care staff if they feel that they need any adjustment of the message.

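### The only planned cost-effectiveness ratio is per nonattendance avoided, but no listed outcome measures attendance

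*Protocol article*

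**What the plan says.** The economic plan is a short passage in the Protocol article, placed under Subgroup Analysis Planned. For the cost side it says: "The direct and indirect costs of implementing this service will be examined through the prospective collection of staff time and resource requirements". For the ratio it says: "The cost effectiveness of the approach will be calculated through incremental cost-effectiveness ratios of costs per nonattendance avoided".

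Under Primary and Secondary End Points, the primary outcomes are service use and healthy days, itemised as psychiatric admission, time to next hospitalization, time in hospital and healthy days. For the rest: "The secondary outcomes are service use, coercive incidents, medication, adverse event, satisfaction with care, intervention, and the trial, social functioning, and economic factors". Table 2 sets these out row by row, and its note gives the sources: "The outcomes will be based on register data [30,31] and patients’ subjective evaluations".

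Statistical Tests then names a single primary outcome: "The primary outcome will be relative risk of admission to psychiatric inpatient services (Table 2". It also plans nonparametric bootstrap methods for skewed cost data.

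Appointments do feature in the intervention. Under Intervention Group, "patients will choose text message content areas related to their medication and follow-up appointments".

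**The concern.** A cost-effectiveness ratio divides a difference in cost by a difference in effect. The plan fixes the effect as missed appointments avoided, and the same document's itemised outcome list does not contain it. The economic sentence and the outcome table therefore disagree.

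If the plan is followed literally, two things can happen. The ratio may not be produced, because no listed outcome supplies its denominator. Or someone must decide after the event what counts as a nonattendance, over which appointments and from which source. The trial is open-label and the messages themselves concern appointments, so an attendance measure defined late is more exposed to selective choice than one fixed in advance.

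**Working it through.** **1. Is attendance among the listed outcomes?** Every place in the article that lists outcomes was compared with the ratio's unit.

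| Place in the Protocol article | What is listed | Attendance? |
|---|---|---|
| Abstract, Methods | The four primary items; secondary outcome headings | No |
| Primary and Secondary End Points | The same items and headings | No |
| Table 2, primary rows | Psychiatric admission; time to next hospitalization; time in hospital; healthy time | No |
| Table 2, secondary service use | Type of admission; involuntary treatment and its length; general hospital treatment and length of stay; private care | No |
| Table 2, satisfaction rows | Satisfied with care; asked to stop messages; left the study early | No: these concern care, messages and the trial |
| Table 2, remaining rows | Coercion, medication, adverse events, quality of life, disability support, direct and indirect cost | No |
| Statistical Tests | Relative risk of psychiatric admission as primary | No |

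Attendance occurs elsewhere only as a message topic (Abstract; Intervention Group) and in the Introduction, which says that telephone calls and letters may reduce nonattendance.

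**2. Can the planned ratio be bounded?** No. The article gives no nonattendance rate, no expected difference and no way of measuring it, so no range can be computed for cost per nonattendance avoided.

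**3. Which effect does the article quantify?** Only hospital admission. The inputs, from Sample Size and Power Calculations, are 65% in controls, a reduction of five percentage points (so 60%), 80% power, two-sided 5%, and 1511 per arm.

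Reproducing the plan's figure for two proportions, with mean proportion (0.65 + 0.60)/2 = 0.625:

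- n = [1.960 × √(2 × 0.625 × 0.375) + 0.842 × √(0.65 × 0.35 + 0.60 × 0.40)]² / 0.05² = 1471 per arm.
- With the continuity correction, n/4 × [1 + √(1 + 4/(n × 0.05))]² = 1511 per arm, an exact match.
- Relative risk = 0.60/0.65 = 0.923, which agrees with the stated 0.92.

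**4. The denominator if the ratio used admission, at that effect.**

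- Risk difference: 0.65 − 0.60 = 0.05, or 5 fewer patients admitted per 100.
- Between arms of 1511: 0.05 × 1511 = 75.55, about 76 fewer patients with any admission.
- Patients treated per patient with an admission avoided: 1/0.05 = 20.
- The ratio is therefore 20 times the incremental cost per patient. The article gives no cost, so for illustration only: assumed costs of €50, €100 and €200 per patient give €1000, €2000 and €4000 per patient with an admission avoided.

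The 76 is a difference between arms in patients admitted at least once. It is not a count of admission episodes, since one patient may be admitted more than once.

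**The case against.** **Not listed is not the same as not collected.** A reader might infer that attendance data will not exist. The article does not support that. Table 2 is a dummy reporting table, not a data-collection form, and the article plans to gather things outside it, such as staff time and nurses' opinions. Service use is a broad heading, and the registers may hold outpatient contacts. A condensed article may also leave the source of a secondary economic measure to a fuller document. This stands, and it limits the point to what is listed. It does not remove the mismatch, because the article itself states both the ratio's unit and an item-by-item outcome list without that unit.

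**The ratio need not use the powered outcome.** A reader might infer that it must. Nothing requires this. Appointments are a direct target of the messages, so nonattendance is a reasonable effect unit. The fault is that it is undeclared as an outcome, not that it is irrelevant. Admissions will also be reported separately, so a favourable attendance ratio would not hide a null primary result.

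**Masking reduces the risk from a late choice.** Allocation Concealment says that outcome assessors and analysts will be blinded. That helps, but it does not define the measure.

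**A switch to admission has its own difficulty.** The article describes costs of implementing the service, while Table 2 lists direct and indirect costs without saying what they contain. If inpatient care is among them, hospital use enters both numerator and denominator. This stands and is taken up in the fix.

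**Conclusion.** The point holds as a mismatch within the article: the effect unit of its only cost-effectiveness ratio is not supplied by any listed primary or secondary outcome. As written, the ratio cannot be formed from those outcomes, and its size cannot be bounded because no attendance figure is given. Whether attendance could be obtained from the registers cannot be told from the article.

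The 76 patients describe the denominator of the suggested replacement, not the size of the defect. They assume the plan's own 65% and 60%, and full arms of 1511.

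The consequence is confined to the secondary economic analysis. The primary analysis and the sample size do not change. It should be put right before data are analysed.

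**What to change.** Replace the effect unit in the cost-effectiveness sentence. Express the ratio as incremental cost per patient with a psychiatric admission avoided at 12 months, using the Table 2 outcome, with an interval from the bootstrap already planned for skewed costs. Cost per psychiatric hospital day avoided could be added. In that case confirm that the primary time-in-hospital row means psychiatric days, as the separate row "Length of general hospital stay (days") suggests. Stratifying the bootstrap by ward, to match randomization within ward, is optional.

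In the same place, state whether the numerator is the cost of running the message service alone or also includes inpatient care, so that it is clear whether hospital use counts on both sides.

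If the sponsor wants to keep cost per nonattendance avoided, add attendance to Table 2 as a secondary outcome, with a definition (which appointments, over what period, what counts as missed) and a named data source.

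The first route costs about two sentences in the protocol and analysis plan and needs no new effect data, because admission is already a planned outcome from routine data. If inpatient care enters the numerator, its costing must be specified. The second route costs a new outcome definition and, if the registers do not hold missed appointments, a further source of data.
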